### Analysis

Data analysis will be carried out with SAS® statistical analysis software (Version 9.2, SAS Institute Inc., Cary, USA). Results will be expressed with their 95% confidence intervals. All statistical tests were two sided p-value less than 0.05 regarded as significant. An intention-to-treat analysis will first be performed on all of the participants. This analysis may be supplemented with a per-protocol analysis involving the participants for whom the follow-up adhered to the protocol, therefore excluding all deviations from the protocol (see above Table
1).

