##### Training program

The training program involves five weekly sessions of 90 min each. The sessions are led by a physiotherapist from the Centre Médico-Chirurgical et de Réadaptation des Massues – Croix Rouge Française, in a rotating manner in order to limit the therapist effect. The patients meet in a group of eight to ten persons.

Each rehabilitation session is composed of three parts: first, a warm-up (15 min) with rhythmic exercises and changes in rhythm (walking forward, backward, on tiptoe, on heels, and so on); second, a period for stretching and mobilizing the rachis (60 min) including relaxation of the lumbar rachis and stretching of the hamstrings, gluteals, quadriceps, psoas and adductors, as well as pelvic tilt awareness exercises; and finally, a third part involving respiratory and postural work (15 min).

The program was conceived in a spirit of continuity and progression from one session to the next. A patient is therefore not allowed to pursue the program in case of absence (except for session 3 or session 4, which are very similar to each other, so one of these sessions can be substituted for the other).

The aims of the training program are: 1) to improve the patient’s knowledge and management of his back through practical education and theoretical explanations; 2) to lessen motor inhibition and the fear of movement through the use of simple, repeated exercises, in the aim of leading the participants toward awareness of their avoidance behavior and encouraging them to resume physical activity; 3) to reinforce global postural control and proprioceptive control; and 4) to raise awareness of factors that can modulate pain.

The physiotherapist emphasizes the purpose of each exercise and also suggests personalized exercises. The aim is to explain techniques and assist participants in their practical acquisition, so that the participants can learn to know and maintain their back.

The training sessions are carried out on the workplace site of the participants in a room that is appropriate for floor exercises.

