##### Assessment of the operational model

Each participant among the thirty or so recruited for this portion of the study will relate his experience of the program during the individual interviews. The experience of the occupational health physicians and of the physiotherapists will also be collected through discussion groups. The program’s elements of satisfaction/dissatisfaction as well as feasibility/acceptability will be studied using the thematic analysis of the content of these interviews and discussion groups.

**Table 1 T1:** Management of protocol violations

**Type of protocol violation**	**Definition**
1. Erroneous inclusions	
2. Poor compliance with the global program sessions	Only one absence, to either session 3 or session 4 of the training program, is tolerated from among the 6 sessions of the global program. In other cases, participants are invited to make up the sessions with another group, in order to limit “program withdrawals.” In the case of an incomplete program, the participants in the intervention group are considered to be non-compliant and deviating from the protocol.
3. Non-attendance at follow-up visits	Participants who do not attend the annual checkups with the occupational health physician of their workplace or the final physiotherapy assessment are first reminded by mail, then by telephone if necessary. It is important to have access to main criterion data for all participants in order to proceed to intention-to-treat analysis.
4. Early withdrawal	This can take place by decision of the participant or following the occurrence of an adverse event that calls into question his participation in the study. Withdrawn participants are not replaced.
5. Missing data concerning the primary outcome (sick leave related to low back pain episode)	These participants cannot be taken into account in the analysis of data.

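### The optional per-protocol analysis uses an exclusion that only the intervention arm can meet and that a recurrence may cause, so it may favor the program

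*Protocol article*

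**What the plan says.** The Analysis section puts intention-to-treat first: "An intention-to-treat analysis will first be performed on all of the participants". It then adds an option: "This analysis may be supplemented with a per-protocol analysis involving the participants for whom the follow-up adhered to the protocol". The same sentence defines the set by what it leaves out ("therefore excluding all deviations from the protocol") and points to Table 1.

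Table 1 lists five types of violation: erroneous inclusion, poor compliance with the sessions, non-attendance at follow-up, early withdrawal, and a missing primary outcome.

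- **Row 2 (session compliance)** is tied to one arm: "In the case of an incomplete program, the participants in the intervention group are considered to be non-compliant and deviating from the protocol". The tolerance is narrow: "Only one absence, to either session 3 or session 4 of the training program, is tolerated", out of six sessions. In other cases participants are invited to make up sessions with another group. The Training program section is stricter in tone: "A patient is therefore not allowed to pursue the program in case of absence", with an exception for sessions 3 and 4.
- **Row 3 (follow-up)** covers "Participants who do not attend the annual checkups" with the occupational health physician, and also those who miss the final physiotherapy assessment, which is the 18-month visit.

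The Follow-up visits section, including its outcome definitions, defines a recurrence as a new low back pain episode that leads to sick leave. It gives three time origins: the end of the program (primary outcome), the beginning of the program (intervention-arm follow-up) and randomization (control-arm follow-up).

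**The concern.** Controls have no program to complete, so row 2 can never remove a control. In the intervention arm it removes people for what happens after randomization, and that may be the outcome itself: someone on sick leave for back pain is likely to miss sessions held at work. A control with the same sick leave stays in. Those who complete the program may also differ from the rest in motivation or prognosis.

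Row 3 adds a separate problem. The 18-month physiotherapy visit measures impairment, disability, psychological scores and quality of life. The primary outcome rests on sick-leave dates available to the occupational health physicians and on reasons learned at the annual checkups. Someone whose primary outcome is fully known would still leave the per-protocol set for missing the physiotherapy visit.

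At stake is how the supplementary result is read. If it looks better than intention-to-treat, part of the difference could come from who was removed.

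**Working it through.** **The plan's own figure.** The document gives no per-protocol figure, so I checked the sample size to fix the planning rates. I read the 25% reduction as relative, 45% to 33.75%, with two-sided 5% and 80% power. The mean rate is 0.39375.

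n = [1.96·√(2·0.39375·0.60625) + 0.8416·√(0.45·0.55 + 0.3375·0.6625)]² / 0.1125² = 295 per group.

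With a continuity correction this is 313; with 34% in place of 33.75% and no correction it is 309. The stated 310 is consistent with these. A drop of 25 percentage points would need only 54 to 62 per group. The planned effect is therefore 11.25 points.

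**Bias when the window includes the program.** Assumptions: no true effect, 45% risk over 24 months, constant hazard, a clock starting at randomization or program start, and a program of two months that begins when the clock does.

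- Hazard: h = −ln(0.55)/24 = 0.0249 per month.
- Risk during the program: 1 − exp(−2h) = 4.9%, or about 15 of 310.
- If a fraction f of these people is excluded, e = 0.0486·f and the per-protocol risk is (0.45 − e)/(1 − e).
- False benefit is the chance of significance in the program's favor in a two-sided 5% test (nominal 2.5%), by the normal approximation, with 325 controls (650/2) and 325·(1 − e) in the intervention arm.

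| f | Intervention risk | Difference from 45% | False benefit |
|---|---|---|---|
| 25% | 44.3% | 0.7 points | 3.7% |
| 50% | 43.6% | 1.4 points | 5.4% |
| 75% | 42.9% | 2.1 points | 7.6% |
| 100% | 42.2% | 2.8 points | 10.6% |

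The difference runs from 0.7/11.25 = 6% to 2.8/11.25 = 25% of the planned effect. The last row is an upper bound for this mechanism, because it assumes that nobody who recurs makes up the missed sessions.

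**Bias when the window opens at program end.** With a constant hazard shared by all, those excluded have the same later risk as everyone else (45%), so the bias is zero. Bias then needs a difference in later risk. As an illustration, assume a persistent gamma frailty with variance 1 and 45% risk over any 24 months. Then λ = (1/0.55 − 1)/24 = 0.0341, and the risk in months 2 to 26 among those without an early recurrence is 1 − (1 + 2λ)/(1 + 26λ) = 43.4%, against 45% for all.

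**General form.** If a fraction e with later risk r is excluded, the per-protocol risk is (0.45 − e·r)/(1 − e). The document gives neither value, so these are assumed:

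| e | r | Intervention risk |
|---|---|---|
| 5% | 65% | 43.9% |
| 10% | 65% | 42.8% |
| 10% | 80% | 41.1% |
| 20% | 80% | 36.3% |
| any | 45% | 45.0% |
| 10% | 35% | (0.45 − 0.035)/0.9 = 46.1% |

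The last row shows the bias running against the program, as it would if people stopped because they felt well.

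**The case against.** A reader might infer that the per-protocol set removes people from the intervention arm only and is biased toward benefit by construction. The documents do not support that.

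- Four of the five Table 1 types can exclude controls as well. Only row 2 is one-sided, which is hard to avoid when a program is compared with usual care. This stands, but exclusions shared by both arms do not cancel a one-sided one.
- Make-up sessions mean that a short sick leave need not end in exclusion. This weakens the mechanism. It does not remove it, since Table 1 still provides for incomplete programs.
- The primary outcome counts recurrences after the program ends, so on that wording a sick leave during the program is not a primary event, and under a constant hazard the bias vanishes. This is the strongest objection. It is limited by the same section, which starts intervention-arm follow-up at the beginning of the program, and by the Background, which names a previous history as the main risk factor for recurrence. That makes equal later risk doubtful.
- The analysis is optional and no decision rule depends on it. That stands and limits the weight of the point. Any suggestion that it would be used to rescue a null result is speculation.

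**Conclusion.** The point holds in a limited form. The asymmetry is built into Table 1; the direction of bias is not. Bias toward the program is plausible because the event that defines a recurrence is also a reason to miss sessions, but direction and size depend on why sessions are missed, how often they are made up, and which time origin applies.

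Through program-period recurrences alone, the distortion is 0.7 to 2.8 points if the clock starts at or before the program, and nil if it starts at program end with a homogeneous hazard. Selection on motivation or prognosis would come on top, in a direction that the document does not fix. The row 3 exclusion of people with a known primary outcome has no evident justification in either arm. The intention-to-treat comparison is untouched by these exclusions, so this is an improvement worth making and not a threat to the primary conclusion.

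**What to change.** 1. Reconcile the three start dates in the Follow-up visits section and count the outcome from one common origin in both arms. The size of the bias cannot be settled before this is done.
2. Make the supplementary compliance analysis a complier average causal effect estimate, with randomization as instrument and all randomized participants with outcome data kept. In its simplest form it is the intention-to-treat risk difference divided by the proportion of the intervention arm who received the program. In the no-effect scenario above the numerator is 45% − 45% = 0 whatever the reasons for absence.
3. Define receipt as program completed according to Table 1 and, as a sensitivity analysis, as any session attended. The Education program section hands out The Back Book at the opening information session and cites evidence that it works, so partial attenders may benefit. If they do, an estimate based on full completion alone would overstate the effect in completers. The Abstract places the booklet at the end of the program, so this should be settled too.
4. If a per-protocol set is kept, label it exploratory, do not exclude participants with a known primary outcome for missed visits, and weight by the inverse probability of completion given baseline predictors.

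The cost is a few sentences of analysis wording and one extra model. The downsides are a wider confidence interval (about 1/0.9 = 1.11 times as wide if, say, 90% complete) and reliance on the assumption that assignment has no effect without receipt.

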#### Follow-up visits

All of the participants were followed for two years: either for the two years following the beginning of the global program for those in the intervention group, or for the two years following randomization for those in the control group. This monitoring was provided by the occupational health physician in the participant’s workplace (one appointment after 12 months and the other after 24 months) and by a physiotherapist from the Centre Médico-Chirurgical et de Réadaptation des Massues – Croix Rouge Française (one appointment after 18 months).

During the 12-month follow-up visit, the intervention group members participating in the evaluation of the operational model of the PRESLO study underwent a semi-structured interview with a member of the research team, immediately following the evaluation by the occupational health physician.

Participants’ presence at follow-up visits and sessions is continually verified using the attendance sheets transmitted by the physiotherapists. Participants who miss an assessment or an appointment are reminded by the Clinical Research Assistant from the data coordinating center concerning their participation in the study or questioned regarding their reasons for absence.

Outcomes

Primary outcome

Percentage of participants with at least one recurrence of low back pain in the two years following the end of the global program.

Secondary outcomes

1. Average time to recurrence of low back pain during the study period.

2. Percentage of participants with a sick leave related to a chronic low back pain (pain for more than three months) in the two years following the end of the global program.

3. Evaluation of the compliance of the participants in the global program.

4. Feedback from the participants in the global program.

5. Feedback from the health care professionals providing the program (physiotherapists and occupational health physicians).

A recurrence is defined as a new episode of low back pain leading to a sick leave. The occupational health physicians of each workplace have access to the date and duration of the work interruptions declared for each participant and can learn the motives from the participant at the annual checkups. The collection of information regarding low back pain recurrence will therefore be comprehensive.

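### The optional per-protocol analysis drops participants in either arm for missing the 18-month physiotherapy assessment, even when their primary outcome is fully known

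*Protocol article*

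**What the plan says.** Under Analysis, the protocol article puts intention-to-treat first and makes the per-protocol analysis an option: "An intention-to-treat analysis will first be performed on all of the participants. This analysis may be supplemented with a per-protocol analysis". The same section limits the supplementary set to participants with adherent follow-up, "therefore excluding all deviations from the protocol", and points to Table 1 for what counts as a deviation.

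Table 1 (management of protocol violations, under Assessment of the operational model) has five items. Three matter here.

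- Item 2, incomplete attendance at the program sessions, concerns one arm: "the participants in the intervention group are considered to be non-compliant and deviating from the protocol".
- Item 3, non-attendance at follow-up visits, names no arm and covers two kinds of visit: "Participants who do not attend the annual checkups with the occupational health physician of their workplace or the final physiotherapy assessment are first reminded". Reminders go out by post and, where needed, are followed by a call.
- Item 5, missing primary outcome data, has its own consequence: "These participants cannot be taken into account in the analysis of data".

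Under Follow-up visits, the occupational health physician sees participants at 12 and 24 months and the physiotherapist at 18 months. A recurrence is a new low back pain episode that leads to sick leave. For its collection, the occupational health physicians "have access to the date and duration of the work interruptions declared for each participant". The reasons for leave are learned from the participant at the annual checkups.

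**The concern.** A per-protocol analysis is normally read as the comparison among participants who were eligible and received what was planned. Here an exclusion is tied to a visit that has nothing to do with eligibility, receipt of the program or measurement of the primary outcome. It reaches controls, and also intervention participants who completed every session.

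Two things are at stake. First, participants with a usable primary outcome are discarded. Second, the exclusion depends on something that happens after randomization and that the outcome might influence: a recurrence is itself an absence from work for back pain, and someone on such leave around month 18 may be less likely to attend. If that happens, the retained recurrence percentages are distorted, and a gap between the per-protocol and intention-to-treat results cannot be attributed to program receipt alone.

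**Working it through.** **Step 1. Does the rule reach the 18-month visit?** The only physiotherapist follow-up visit described is at 18 months, so the final physiotherapy assessment in Table 1 item 3 is that visit. The Analysis section excludes every Table 1 deviation, so missing the visit (after the reminders) excludes the participant. Item 2 is limited to the intervention group and item 3 is not.

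**Step 2. Does that visit feed the primary outcome?**

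| Source | What it supplies |
|---|---|
| 18-month physiotherapy visit (Other parameters) | Impairments, functional disability, working conditions and job satisfaction, anxiety and depression, fear-avoidance, coping, quality of life, quality of exercise execution |
| Occupational health records (Outcomes) | Dates and durations of work interruptions |
| Annual checkups at 12 and 24 months (Outcomes) | Reason for each interruption |

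The primary outcome needs the second and third rows only. A missed annual checkup is different, because it can leave the reason for a leave unknown and so the outcome undetermined. That case overlaps with item 5.

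**Step 3. The plan's own sample size.** Inputs from Number of subjects required: 45% control rate, 25% reduction, 310 per group, 80% power, 5% type 1 error. The test is two-sided (Analysis). Read as a relative reduction, the intervention rate is 0.45 × 0.75 = 0.3375. The two-proportion formula gives 295 per group without continuity correction and 313 with it, so 310 is reproduced within about 1% by the corrected version. 620 × 1.05 = 651, which matches 650.

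**Step 4. Power if participants are removed at random.** With d = 0.1125, p̄ = 0.39375 and n per arm (no continuity correction):

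power = Φ{[d − 1.96·√(2p̄(1−p̄)/n)] / √[(0.45·0.55 + 0.3375·0.6625)/n]}

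- n = 310: 81.9%.
- The plan's 5% allowance applied in full to the 650: 650 × 0.95 / 2 ≈ 309 per arm, power 81.8%.
- Outside the plan's figures, 15% removed from 310 (263.5 per arm) gives 75.4%, and 30% removed (217 per arm) gives 67.1%. Both removal rates are assumptions without support in the document.

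**Step 5. Selection if attendance depends on recurrence.** Let m₁ and m₀ be the probabilities of missing the visit with and without a recurrence. The document gives neither, so all values below are assumed. The rate among those retained is p(1−m₁) / [p(1−m₁) + (1−p)(1−m₀)].

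*Same pattern in both arms*, m₁ = 0.25, m₀ = 0.10:

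- Control: 0.3375 / (0.3375 + 0.4950) = 40.5%.
- Intervention: 0.2531 / (0.2531 + 0.5963) = 29.8%.
- Risk ratio 0.735 against the true 0.75. The odds ratio stays at 0.623, because selection on the outcome alone, equal in both arms, cancels from it.

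*Different pattern by arm*, m₁ lowered to 0.15 in the intervention arm only:

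- Intervention: 0.2869 / (0.2869 + 0.5963) = 32.5%.
- Risk ratio 0.325 / 0.405 = 0.80.

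*No true effect* (45% in both arms), m₁ = 0.20 in one arm and 5% for everyone else: 40.8% against 45%, a spurious difference of about 4.2 points. The risk ratio is about 0.91 or 1.10, depending on which arm is affected.

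A material bias in the comparison therefore needs an attendance pattern that differs by arm. If missing the visit is unrelated to recurrence, there is no bias, only the small loss in step 4.

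**The case against.** The strongest case against is that little depends on this analysis. It is optional, follows intention-to-treat, and carries no power claim or decision rule. Defining a per-protocol set by follow-up as well as by treatment is a recognisable choice, here applied to both arms, and any such set conditions on post-randomization events. Reminders shrink the group concerned. Only item 2 calls participants deviating from the protocol in so many words, and the full protocol or analysis plan may say which missed visits count.

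The points on consequence stand in full. They do not change what the article states: the set is defined by follow-up adherence and refers to the whole of Table 1, so this is a stated rule and not an omitted detail. Item 3 gives securing the main outcome data as the reason for pursuing absentees, and excluding people who have those data does not serve that aim.

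Three stronger readings are tempting and are not supported.

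- A reader might infer that anyone who misses any follow-up visit is wrongly discarded. Because reasons for leave are learned at the annual checkups, a missed 12- or 24-month visit can leave the outcome undetermined. The point holds for the 18-month visit.
- A reader might infer a serious loss of power, to 75% or 67%. Those figures need 15% or 30% removed, while the plan allows 5% for missed appointments and early dropouts together.
- A reader might infer that the rule moves the risk ratio from 0.75 to 0.80. That needs an assumed difference between arms for which the document gives no basis. With the same pattern in both arms the risk ratio is 0.735 and the odds ratio is unchanged.

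**Conclusion.** The point holds in a narrow form and is minor. As written, a participant in either arm with a determined two-year outcome leaves the per-protocol set for missing only the 18-month physiotherapy assessment, a visit that contributes nothing to that outcome. Item 5 already deals with participants whose outcome is missing, so item 3 is not needed for that purpose.

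That recurrence might affect attendance is an inference from the outcome being a sick leave; there are no attendance data to test it. It is most plausible for leave that coincides with the appointment, whereas the outcome counts any recurrence over two years. The calculations of selection are illustrations and not estimates of what will happen in this trial.

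**What to change.** Add one sentence to the Analysis section: for the per-protocol analysis of the primary outcome, a missed 18-month physiotherapy assessment alone does not exclude a participant whose recurrence status has been determined, including the motive of each leave; it affects only the measures taken at that visit.

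The condition on motive is essential. A leave record with dates and durations alone does not show whether the leave was for low back pain, so availability of a record is not enough. Participants who miss an annual checkup and whose motive for leave remains unknown continue to be handled under Table 1 item 5.

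The cost is that sentence. It needs no new data and no further participants, and it changes no stated figure.
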